##### Criteria for developing a practice guideline

We have used both the criteria developed by Grimshaw and Shaneyfelt as the basis for formulating our guidelines.[1,2]

##### Systematic review of the literature

Utilizing the Alberta Research Centre for Child Health Evidence (ARCHE), we carried out a systematic literature review to ensure we had identified all primary published studies addressing the management of children with croup. We have completed a draft of the guidelines.

##### Remaining steps prior to completion of croup clinical practice guideline

When the guidelines are in final form, a parents' group will critically review the guidelines for clarity and content. As well, the guidelines will be reviewed by a randomly selected group of family physicians for clarity and clinical relevance. Once development of the guidelines is complete, we will seek endorsement by the Canadian Pediatric Society and the Canadian Association of Emergency Physicians. We will also submit the guidelines to the Canadian Medical Association Journal for publication.

#### The three intervention strategies

The intervention strategies to be compared will be a) mailing of printed educational materials (PEMs) (low intensity intervention); b) mailing PEMs plus a combination of interactive educational meetings, educational outreach visits, and reminders (intermediate intensity intervention); and c) mailing PEMs, interactive sessions, outreach visits, reminders plus identification of local opinion leaders (high intensity intervention.

##### Low intensity intervention

The low intensity intervention is the current strategy utilized by the *Alberta Medical Association Clinical Practice Guidelines Program *for disseminating new guidelines. This intervention arm will serve as a "control". The Croup Guidelines will be mailed to each physician registered with the *Alberta College of Physicians and Surgeons*. The Guidelines will also be available on the *Alberta Medical Association Clinical Practice Guidelines Website*.

##### Intermediate intensity intervention

The intermediate intensity intervention utilizes techniques that have consistently shown at least a moderate impact on professional behavior. We will work through existing organizational structures in order to more closely simulate how the *Alberta Medical Association Clinical Practice Guidelines Program *might disseminate future guidelines. More specifically, the *Alberta Medical Association Clinical Practice Guidelines program *and the Croup clinical practice guideline committee will work with the Universities of Calgary and Alberta Continuing Education Programs to develop an interactive educational program for physicians, nurses, and respiratory therapists. Utilizing the existing Continuous Quality Improvement Staff in each Health Region, each hospital's admitting physicians, acute care nurses and respiratory therapists will be invited to participate in the interactive educational program carried out by one of the Croup Clinical Practice Guideline Committee members. A "local champion" will also be identified. They will conduct educational outreach visits to physicians, nurses, and respiratory therapists who did not attend the interactive educational program.

##### High intensity intervention

The high intensity, intervention utilizes a multi-faceted approach described by Lomas.[3] This approach uses a variety of techniques, including interactive educational meetings, educational outreach visits, reminders, identification of local opinion leaders and establishment of a local consensus process. The physician-focused multi-faceted dissemination strategy will involve identification of physician "opinion leaders" at each hospital randomized to this arm. All physicians with admitting privileges to a hospital will be asked to complete a validated questionnaire for the purpose of identifying the "local opinion leader".[4] All "opinion leaders" will be invited to participate in a workshop on the evidence for the practice guideline's recommendations and on basic principles of behaviour change.

### Planned inclusion/exclusion criteria

#### Health care utilization using administrative databases

Alberta Health and Wellness, a branch of the Alberta provincial government, is the custodian of several data sources that are accessible for research purposes. These databases can be linked, and are considered to be of good quality with reliable personal identifiers on more than 95% of records. Through collaboration with the Project Coordinator, Health Surveillance Branch, Alberta Health & Wellness, we extracted the data specified below from the Canadian Institute for Health Information Hospital Inpatient database, Alberta Ambulatory Care Classification System, the Alberta Health Care Insurance Plan (AHCIP) Payment Database, and the AHCIP Registry Dataset.

All children 0–6 years of age and 6–16 years of age who are Albertan residents, and who have been evaluated and diagnosed by an Albertan physician to have croup (*ICD-9-CM 464.1 Acute Tracheitis, 464.2 Acute Laryngotracheitis, and 464.4 Croup, either as a primary or secondary diagnosis*) have been included in our utilization data.

##### Methodological assignment of physicians to hospital

Encrypted physician identifiers are available for each health care encounter in which a child was diagnosed to have croup. Each of the physicians appearing in our dataset were assigned to a specific hospital based on following: first, the hospital to which they admitted children with croup (62% of physicians); second, the hospital clinic or emergency department at which they diagnosed children to have croup (82% of physicians); or, third, the hospital to which a physician associate admitted or evaluated children with croup (93% of all physicians). (Physicians who shared the same billing address where assumed to be associates.)

#### Adverse outcomes

We have used administrative databases, selected medical record audit, and review of medical examiner cases to establish Alberta morbidity and mortality rates for the six-year baseline. Data gathered from these three sources will allow us to establish the incidence of rare but severe outcomes such as death, anoxic brain injury, and endotracheal intubation.

*Administrative databases *were screened for any children with a diagnosis of croup who died, were intubated (ICD-9-CM 96.04), or were also diagnosed during the same admission to have anoxic brain damage (ICD-9-CM 348.1) or cerebral edema (ICD-9-CM 348.5).

##### Retrospective record audit

We are auditing the medical records of children identified from the administrative databases who met the above criteria. The baseline review is almost complete, and we will repeat the process in follow-up. To double check that our reliance on administrative databases has not resulted in missed patients, we have also reviewed the manual admission logs for Alberta Children's Hospital and the University of Alberta Hospital intensive care units, and will contact the medical records departments at each of the regional medical centers (Medicine Hat, Lethbridge, Red Deer, Fort McMurray, Grande Prairie).

##### Medical examiner's office

We have also contacted the Alberta Medical Examiners' Offices and have arranged for review of children ≤ 16 years of age that died of "respiratory causes".

#### Practice patterns using retrospective medical record audit

Retrospective record audit will be used to establish the extent to which physicians use effective therapies for croup. The baseline review is almost completed, and will be repeated for the follow-up period. Each of the 24 targeted hospitals were asked to generate a list of medical record numbers using standard ICD9 codes as above that identify all children that were hospitalized and/or evaluated in the emergency department with croup. Medical records pertaining to all hospitalized children were (will be) reviewed. Of those children evaluated in the emergency department, a maximum of 30 patients per year were randomly selected and reviewed. For the follow-up record audit, since significant annual change is likely to occur, we will audit up to a maximum of 100 records to allow greater accuracy for our annual estimates.

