#### Costs associated with hospitalization

Though there are no comprehensive studies examining the health care costs of croup, one study suggests that the total 'costs' for hospitalization were almost three times that of the total costs for all ED visits.[23] In the case of bronchiolitis – which likely has a similar costing structure to croup – 62% of all health care expenditures for the disease are expended on the less than 1% of children who are admitted to hospital.[29] Our baseline provincial data for croup shows that the average number of MD visits per disease episode is only 1.15, and that 3.6% of children with croup are hospitalised. Given the relative greater costs associated with hospital admission versus MD visits, or other costs such as medications, it is likely that hospital admissions are the principal determinant of health expenditures. Therefore a substantial reduction in hospitalization rates should substantially reduce health care expenditures for the disease.

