#### Practice pattern data obtained from medical record audit

We are just completing an audit of medical records of children diagnosed to have croup based on ICD9 coding from April 1^st^, 1994 to March 31^st^, 2000. By late 2006, we will repeat an identical audit of medical records of children diagnosed as having croup between April 1^st^, 2000 to March 31^st^, 2006. This timetable for extraction of data provides the above delineated advantages.

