### Proposed primary and secondary outcome measures

The primary outcome will be the rate of hospital days per 1,000 disease episodes. If differences in rate of hospital days between intervention groups are detected, we will explore to what degree they are due to a change in rates of admission versus a change in hospital lengths of stay.

The secondary outcomes will be utilization of appropriate therapies including:

▪ Proportion of patients treated in the emergency department and hospital with a corticosteroid.

▪ Proportion of patients evaluated in emergency department for at least three hours after treatment with corticosteroids before the decision to admit to hospital is made.

▪ Time to treatment with corticosteroids in both emergency department and hospital patients.

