### Proposed analyses

The principal analysis will examine hospital stays arising from individual disease episodes over the six-year baseline and study period. We will apply a linear mixed model (Laird-Ware approach) incorporating random effects for hospital, year within hospital, as well as fixed effects for intervention and year. We will also pursue a more detailed explanatory analysis incorporating individual subject characteristics (age, sex) as well as random effects for admission and discharge physician. Additionally we will develop similar models for length of stay restricting to disease episodes leading to admissions, and mixed effects logistic regression model for admissions. Secondary analyses relating to steroid use and *Telephone OutPatient (TOP) *scores will follow a similar format. The examination of day 1- 3 *TOP *scores will require augmenting the basic model framework to include random subject effects and a serially correlated (within subject) residual error structure. No subgroup analyses are planned.

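### The chart audit takes every admission but a capped ED sample whose cap rises from 30 to 100; with no weighting stated, the pooled corticosteroid proportion depends on the sampling if use differs by setting

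*Protocol article*

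**What the plan says.** The section on practice patterns by retrospective record audit (Protocol article) sets two sampling rules. For inpatients: "Medical records pertaining to all hospitalized children were (will be) reviewed". For the ED: "Of those children evaluated in the emergency department, a maximum of 30 patients per year were randomly selected and reviewed". For the follow-up audit the ED rule changes: "we will audit up to a maximum of 100 records to allow greater accuracy for our annual estimates". Both caps are read here as per hospital per year.

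The section on the timing of the audit describes the April 2000 to March 2006 round differently: "we will repeat an identical audit of medical records of children diagnosed as having croup".

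The first secondary outcome is one line across both settings: "Proportion of patients treated in the emergency department and hospital with a corticosteroid".

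Under Proposed analyses, the principal model is described as "incorporating random effects for hospital, year within hospital, as well as fixed effects for intervention and year". The sentence beginning "Secondary analyses relating to steroid use and" then gives the steroid analyses a similar format. No sampling weight and no ED/inpatient term is named.

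**The concern.** Admitted children enter the audit with probability 1. ED-only children enter with a probability set by the cap and the hospital's volume. A pooled, unweighted proportion therefore gives admitted children far more weight than their share of cases, and that weight changes when the cap changes. If the two groups are treated with steroids at different rates, the audited proportion can move with no change in practice.

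The weight also depends on how many children are admitted, and hospital days, of which admissions are a component, are what the interventions aim to reduce. Part of any arm difference in measured steroid use could then reflect sampling rather than prescribing. Increasing the use of effective therapies is the trial's stated secondary objective. Separately, two sections describe the follow-up audit in incompatible ways.

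**Working it through.** The plan gives no expected proportion, sample size or power for the audit, so there is no figure to reproduce. The check is mixture arithmetic.

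**Inputs from the Protocol article**
- Province: "3.6% of children with croup are hospitalised".
- Baseline utilisation data: 21 admissions per 1,000 episodes at the six largest-volume hospitals (2.1%) and 116 per 1,000 at the 30 smallest (11.6%).
- Volume strata: under 100, 100 to 700, and over 700 cases a year.
- ED caps of 30 and 100; all admissions audited.
- A 25% change is the effect used for power. It refers to hospital days and is borrowed here as an illustrative fall in admissions.

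**Assumptions**
- Steroid use is pH in admitted and pE in ED-only children: 60%/20% as the main case, with 45/20, 30/20 and 20/20 as the range.
- All non-admitted cases are ED cases. Fewer ED cases would shrink the effect.

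**Formulas**, for N cases a year and admission rate a:
- admitted charts h = aN
- ED-only charts e = min(cap, (1-a)N)
- unweighted proportion = (h·pH + e·pE)/(h + e)
- population proportion = a·pH + (1-a)·pE

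**Example**, N = 700, a = 3.6%, so h = 25.2:
- Cap 30: (25.2×0.6 + 30×0.2)/55.2 = 21.12/55.2 = 38.3%. Admitted share of charts 25.2/55.2 = 45.7%.
- Cap 100: (25.2×0.6 + 100×0.2)/125.2 = 35.12/125.2 = 28.1%. Admitted share 20.1%.
- Population: 0.036×0.6 + 0.964×0.2 = 21.4% throughout.

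**Effect of the cap change, practice fixed at 60/20**

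| N | a | Cap 30 | Cap 100 | Population | Shift (points) |
|---|---|---|---|---|---|
| 75 | 11.6% | 29.0% | 24.6% | 24.6% | -4.4 |
| 300 | 11.6% | 41.5% | 30.3% | 24.6% | -11.2 |
| 700 | 3.6% | 38.3% | 28.1% | 21.4% | -10.2 |
| 1,500 | 2.1% | 40.5% | 29.6% | 20.8% | -10.9 |

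At N = 300 and a = 11.6%, the shift is -7.0 points at 45/20, -2.8 at 30/20 and 0.0 at 20/20. A hospital with no more than 30 ED-only cases a year has no shift, because neither cap binds.

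**Effect of 25% fewer admissions, cap constant at 100, 60/20**

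| N | a | Unweighted change | Population change |
|---|---|---|---|
| 300 | 11.6% | -2.0 | -1.2 |
| 700 | 3.6% | -1.7 | -0.4 |
| 1,500 | 2.1% | -1.9 | -0.2 |

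For N = 700: h falls to 18.9, and (18.9×0.6 + 20)/118.9 = 26.4%, against 28.1% before. This takes children no longer admitted to be treated at the ED-only rate. If they keep the 60% rate instead, the population figure does not move. ED-only use becomes (674.8×0.2 + 6.3×0.6)/681.1 = 20.4%, and the unweighted figure is (18.9×0.6 + 100×0.204)/118.9 = 26.7%, a shift of -1.4 points that is all sampling.

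**Effect of weighting.** Giving each ED-only chart the weight (1-a)N/e makes the pooled estimate aN·pH + (1-a)N·pE over N, the population proportion, whatever the cap. It leaves the population change in the last column.

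**The case against.** Four points can fairly be made against this.

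*The cap step is common to all arms.* The second audit round starts in April 2000 and the interventions in August 2003, so on the natural reading the cap rises three years before intervention, in every arm. Fixed year effects absorb its average, and stratifying allocation by volume limits imbalance in the remainder. This stands. A reader might infer that the 10-point shifts above bias the randomised comparison; the documents do not support that. What a common year effect cannot absorb is the hospital-specific part: from zero to about -11 points here, with admission rates ranging from 16 to 287 per 1,000 and not a stratification factor.

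*Direction and size rest on an assumed split.* This also stands. The 22% steroid use reported for 12 smaller hospitals is not divided by setting. A reader might conclude that measured change is biased downward by design, or that the most effective arm is necessarily penalised. Either needs admitted children to receive more steroids than ED-only children. With equal use the shift is zero, and with the reverse gap its sign reverses.

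*Unweighted analysis is inferred.* The article does not say that charts will go unweighted, and setting-specific reporting would be compatible with its list of secondary outcomes, whose second item concerns ED patients only. An analysis plan could add weights. But the sampling rule, the one-line outcome and the model terms are fixed here, and followed as written they give a proportion that depends on sampling.

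*Part of the admission effect is real.* If children no longer admitted are treated at the ED-only rate, the population proportion falls too. Only the excess over that is artefact.

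**Conclusion.** The concern holds conditionally, for a secondary outcome. As written, the audit yields a pooled corticosteroid proportion that varies with the ED cap, hospital volume and admission rate whenever steroid use differs between admitted and ED-only children.

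Under the assumed 60/20 split, the 30-to-100 change moves it by about -4 to -11 points in the scenarios worked, and by less at smaller gaps and at the smallest sites. Its main consequence is that 1994-2000 cannot be compared directly with later years. Between arms there remain two smaller effects: the hospital-specific part of the cap step, and roughly 2 points for a 25% fall in admissions, of which 0.2 to 1.2 is a population change.

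One part needs no assumption: a follow-up audit with a different cap is not identical to the baseline audit, so the two sections must be reconciled. The primary outcome, hospital days from administrative data, is untouched.

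**What to change.** 1. For the pooled secondary outcome, weight each audited ED-only chart by (ED-only croup patients on that hospital's list that year)/(ED-only charts audited), and each admitted chart by 1. The lists cover children admitted, seen in the ED, or both, so count a child admitted through the ED once, as admitted.
2. Report ED-only and admitted children separately as supportive results. Within-setting proportions do not depend on the cap, but admission is itself affected by the intervention, so these comparisons are not fully protected by randomisation.
3. State the cap for each audit year from April 1994 to March 2006, as a per-hospital, per-year figure, and make clear which one applies to April 2000 to March 2003.
4. Replace the description of the second audit as identical with one that names the changed ED cap.

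The cost is small: the denominators come from the hospital lists already requested, and the rest is wording. The downside is a slightly larger variance from the weights.

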#### Clinical outcomes & psychosocial burden using prospective questionnaire

The parents of all children evaluated in, or admitted to each of the 24 hospitals with a diagnosis of croup between September and May during the baseline, intervention, and follow up periods will be approached to participate in a follow up telephone survey by a staff nurse. A log of all children diagnosed to have croup will be maintained to allow the comparison of those children enrolled to those not enrolled.

#### Identification & enrolment of participating hospitals

As noted above, Alberta hospitals were rank ordered based on the number of disease episodes and rates of hospitalization for a six-year period. We then approached in this order each of the hospital administrators and clinical staff for permission to include their hospital in our study until a total of 24 hospitals consented (the staff of 11 hospitals refused to participate for reasons ranging from "anticipated closing of the hospital in the near future" to "too heavy an administrative workload to participate in a study").

### Proposed duration of treatment period

Detailed planning for the intervention strategies will take place between February and July 2003. We will initiate each of the interventions in August, 2003 and conclude them in March, 2004.

### Duration of the baseline and follow-up periods

#### Utilization and adverse outcome data obtained from the administrative datasets

We have extracted data from administrative databases from April 1^st^, 1994 to March 31^st^, 2000, providing six years of data. In summer 2006, we will again extract data from administrative databases from April 1^st^, 2000 to March 31^st^, 2006. Extraction of data across these time periods will allow us to extend the baseline utilization rates from six to nine years. Most importantly, this will ensure no significant changes occur just prior to the study interventions. Extraction of data through March 31^st^, 2006 will provide utilization data for the intervention and two follow-up years.

#### Practice pattern data obtained from medical record audit

We are just completing an audit of medical records of children diagnosed to have croup based on ICD9 coding from April 1^st^, 1994 to March 31^st^, 2000. By late 2006, we will repeat an identical audit of medical records of children diagnosed as having croup between April 1^st^, 2000 to March 31^st^, 2006. This timetable for extraction of data provides the above delineated advantages.

#### Clinical outcome & psychosocial burden data obtained from prospective questionnaire

##### Duration of enrolment

The parents of children admitted to each of the 24 hospitals with a diagnosis of croup during "croup season" (Sept 1^st ^to May 31^st^) from November 1^st^, 2001 and finishing March 31^st^, 2006, will be asked by a staff nurse to participate in a telephone survey.

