## Methods

### Proposed trial design

We will conduct a cluster randomized controlled trial after completing a baseline survey. In order to provide a comprehensive answer as to whether or not our interventions are beneficial, we have obtained data from several different sources. The stages are as follows.

1. Baseline survey (currently near completion):

▪ Utilizing administrative data, we have documented Alberta health care utilization rates.

▪ We are documenting severe adverse outcomes in Alberta utilizing administrative data, and both medical examiner and records audit.

▪ Using this data, we have rank ordered Alberta hospitals based on number of disease episodes and rates of hospitalization.

▪ We have enrolled the highest ranking 24 hospitals who consented to participation.

▪ We are documenting practice patterns in these 24 selected Alberta hospitals utilizing medical records audit.

▪ Utilizing a prospective cohort questionnaire, we are documenting the duration of clinical symptoms of children with croup and the psychosocial burden on their families in the same 24 selected Alberta hospital emergency departments

2. Development of clinical guidelines that address indications for drug therapy and hospital admission/discharge criteria. The process will include:

▪ convening an guideline committee with a range of disciplines and professions;

▪ critically reviewing the published literature;

▪ drafting guidelines which meet standard criteria for developing guidelines;

▪ review of the guidelines by both parents and a wide-range of users (family physicians, nurses, and respiratory therapists);

▪ obtaining approval of the guidelines from the Canadian Pediatric Society, Canadian Association of Emergency Physicians, and the Alberta Medical Association; and

▪ publishing the guidelines in journals such as the Canadian Medical Association Journal.

3. Randomization of 24 Alberta hospitals to one of three implementation strategies.

4. A follow-up survey whose purpose is to detect any change from baseline by:

▪ documenting severe adverse outcomes and utilization rates in Alberta;

▪ documenting practice patterns in the 24 Alberta hospitals surveyed at baseline;

▪ documenting the duration of symptoms of children with croup and the psychosocial burden on their families attending these 24 hospital emergency departments.

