#### Other outcomes

##### Clinical outcomes

To determine which dissemination strategy will most effectively maintain or improve clinical outcomes:

▪ by reducing or maintaining the number of uncommon, severe clinical events such as intubation, respiratory and cardiac arrest, anoxic brain injury, or death.

▪ by reducing, (in a prospective cohort of children enrolled from each hospital) croup symptoms on days 1, 2, and 3 following assessment, as measured by a telephone follow-up

▪ assessment tool (Telephone Out Patient (TOP) score).

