#### Clinical & psychosocial burden outcomes

##### RMO database

We are maintaining a database of all children diagnosed as having croup whose parents refused, were missed, or are otherwise excluded. Demographics and disease characteristics of children and their families in this database will be compared to those families who are administered the survey to ascertain if the two populations are different.

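### The enrolment-duration section states the telephone-survey population as admitted children only, contradicting the inclusion criteria, which take all children evaluated or admitted; if followed, it would select the survey cohort on an event the interventions aim to change

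*Protocol article*

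**What the plan says.** Two sections of the protocol article define who is approached for the prospective telephone survey, in both cases by a staff nurse.

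- Duration of enrolment, which gives the survey's calendar dates: "The parents of children admitted to each of the 24 hospitals with a diagnosis of croup during" the croup season.
- Clinical outcomes & psychosocial burden using prospective questionnaire, within the planned inclusion/exclusion criteria: "The parents of all children evaluated in, or admitted to each of the 24 hospitals with a diagnosis of croup".

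Other sections bear on the same population. Proposed trial design describes the follow-up survey as "documenting the duration of symptoms of children with croup and the psychosocial burden on their families attending these 24 hospital emergency departments", and places the baseline survey in the same departments. RMO database says: "We are maintaining a database of all children diagnosed as having croup whose parents refused, were missed, or are otherwise excluded". The abstract speaks of parents of children with a croup diagnosis and does not mention admission.

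The survey supplies "croup symptoms on days 1, 2, and 3 following assessment, as measured by a telephone follow-up" tool (the TOP score), together with caregiver stress and the child's lost sleep. All of these are listed as other outcomes. It also feeds the economic analysis: duration of symptoms is a named benefit (Potential benefits), and each family's missed work, travel time, parking and ambulance costs are set to the survey means (Costs to the family).

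**The concern.** The two statements cannot both describe the cohort, and the difference is not neutral in this trial. The guideline addresses criteria for admission and discharge. The article defines the main endpoint as follows: "The primary outcome will be the rate of hospital days per 1,000 disease episodes". If the arms differ on it, "we will explore to what degree they are due to a change in rates of admission versus a change in hospital lengths of stay". Admission is therefore a post-randomisation event that the interventions are meant to alter.

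An arm comparison confined to admitted children would compare groups that the intervention itself helped to form. If an effective arm sent home children who would otherwise have been admitted, they would drop out of its survey, and those remaining would tend to be more severely ill. The arm could then look worse on symptoms, stress and sleep although no child did worse. The survey would also miss the families of children newly sent home, although the stated objective is to maintain or reduce family burden.

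The economic analysis would be affected too, because mean family costs from admitted children would be applied to families whose children were mostly never admitted.

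**Working it through.** **1. The sections side by side**

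| Section | Survey population stated or implied |
|---|---|
| Abstract, Methods/designs | parents of children diagnosed with croup |
| Proposed trial design (baseline and follow-up surveys) | families attending the 24 emergency departments |
| Inclusion/exclusion criteria, prospective questionnaire | all children evaluated or admitted |
| RMO database | log of all diagnosed children who were not enrolled |
| Duration of enrolment | admitted children |

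Four places point to the wider population and one to the narrower. The outlier's task is to give dates; the section whose task is eligibility gives the wider group.

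**2. Does the planned survey size show which is meant?**

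Recruitment of families expects 450–500 children in 13 baseline months and about 900 in 24 months.

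450 × 24/13 = 831; 500 × 24/13 = 923.

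The figure of about 900 is consistent with the recruitment rate, but it would be so under either population. It does not settle the matter.

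**3. How far apart are the two populations?**

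Input: 7–31% of children evaluated in an emergency department are hospitalised (Epidemiology & burden of the disease; a literature range, not data from the 24 hospitals).

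Share left out by the narrower wording = 1 − admitted share: 1 − 0.31 = 0.69; 1 − 0.07 = 0.93. So about 69–93%.

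For the family costs, the relevant figure is the Alberta one: 3.6% of children with croup are hospitalised (Costs associated with hospitalization). 100 − 3.6 = 96.4% of the children whose families would be assigned the survey mean were never admitted.

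**4. Direction of the artefact: an illustration only**

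The document gives no severity distribution, so everything in this step is assumed: severity is normal and identical in all arms; the most severe on a latent scale are admitted; symptoms correlate with that scale at rho = 0.3 to 1.0; and admissions fall by 25%. The document's only 25% is the change in mean hospital days used for power. Assigning all of it to admissions is a further assumption.

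Mean symptom severity among the admitted, in SD units, is rho × φ(z)/p, where p is the admitted share and z cuts off the upper p of the normal curve. The spurious shift is rho × [φ(z′)/p′ − φ(z)/p], with p′ = 0.75p.

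| p → p′ | φ(z)/p | φ(z′)/p′ | Shift, rho 0.3 to 1.0 |
|---|---|---|---|
| 3.6% → 2.7% (Alberta average) | 2.197 | 2.309 | 0.03 to 0.11 SD |
| 11.6% → 8.7% (30 smallest-volume hospitals) | 1.684 | 1.820 | 0.04 to 0.14 SD |
| 31% → 23.25% (top of the literature range) | 1.138 | 1.314 | 0.05 to 0.18 SD |

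With all evaluated children surveyed, the shift from this source is 0 in every row. Under these assumptions the artefact is small and runs against the arm that admits fewer children. Larger enrolment would not remove it.

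**The case against.** The strongest reply is that the article already settles the population. Eligibility belongs to the inclusion criteria, and a sentence under a heading about duration should not be read as redefining it. The instrument also fits the wider group: it is named as an outpatient score, it covers days 1–3 after assessment, and the first call comes within 24 hours of enrolment, whereas the median hospital stay is given as 48 hours. Forms go to one study coordinator, and a log of all diagnosed children is kept, so a hospital that enrolled only admitted children could be noticed. This stands: the narrower sentence is most likely a slip, and any bias depends on its being followed.

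That does not remove the contradiction. Both sentences are current text, both describe a staff nurse approaching parents, and 24 hospitals have to apply one rule.

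A reader might go further in four ways that the document does not support.

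- That the cohort is selected by the primary outcome itself. The primary outcome is a rate of hospital days that also reflects length of stay; admission is one component.
- That the survey is already biased. By October 2002, 170 children had been recruited, and nothing says that any hospital restricted enrolment to admitted children or that nurses worked from the enrolment-duration sentence.
- That a fall in admissions would remove exactly the mildest quarter of admitted children. No section projects a 25% fall in admissions or says which admissions would be avoided.
- That the trial's main result is at risk. The primary outcome comes from administrative data and the secondary outcomes from record audit.

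**Conclusion.** The contradiction is real and the point holds, conditionally. Followed as written, the enrolment-duration sentence would restrict the survey to children selected on a post-randomisation event that the interventions aim to reduce. It would leave out about 69–93% of children evaluated in emergency departments, if the literature range applies to these hospitals.

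What would be affected is limited to the other outcomes (TOP score, caregiver stress, lost sleep) and the survey-based economic inputs (symptom duration and mean family costs).

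The size of any bias cannot be derived from the document; the standard-deviation figures above show direction and rough order under assumed inputs. The correction is worth making because these outcomes are the trial's check that fewer admissions do not cost children or families anything.

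**What to change.** Reword the sentence under Duration of enrolment so that it names the population in the inclusion criteria: parents of all children evaluated in or admitted to the 24 hospitals with croup, whatever the disposition. Keep its dates and season as they are.

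State that the between-arm comparison of the survey outcomes, and the survey means used in the economic analysis, are taken from that whole cohort and not from admitted children only.

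The cost is one reworded sentence, one added sentence and a reminder to the recruiting nurses. No sample-size or power figure changes. The log of diagnosed children that the article already plans can be used to confirm that children sent home are being approached.
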